#### Reporting procedures for adverse events/serious adverse events

All AEs and SAEs will be recorded, logged, and monitored by the PI and TMG. If an AE is reported more than once for a participant, or more than three times during the study, it will be treated as an SAE.

A serious adverse event (SAE) occurring to a participant will be reported to the REC that gave the favourable opinion of the study where in the opinion of the Chief Investigator the event was ‘related’ (resulted from administration of any of the research procedures) and ‘unexpected’ in relation to those procedures. Reports of related and unexpected SAEs will be submitted within 15 working days of the Chief Investigator becoming aware of the event, using the HRA report of serious adverse event form.

In the event that a complaint is received from a participating parent or child, the therapists, or their managers, the CI will attempt to resolve the issue as far as is possible. If this is not possible, and the issue remains unacceptable to participants, formal complaints will be logged and dealt with by the sponsor’s representative in liaison with the CI. Those indicating an AE or SAE will be logged accordingly.

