### Adverse event reporting and harms {22}

#### Definition of serious adverse events

A serious adverse events (SAE) is any untoward medical occurrence that:Results in deathIs life-threateningRequires inpatient hospitalisation or prolongation of existing hospitalisationResults in persistent or significant disability/incapacityConsists of a congenital anomaly or birth defect

Other ‘important medical events’ may also be considered a serious adverse event when, based upon appropriate medical judgement, the event may jeopardise the participant and may require medical or surgical intervention to prevent one of the outcomes listed above.

NOTE: The term ‘life-threatening’ in the definition of ‘serious’ refers to an event in which the participant was at risk of death at the time of the event; it does not refer to an event which hypothetically might have caused death if it were more severe.

There is a very low risk of SAEs in the current trial; however, the following details a non-exhaustive list of potential SAEs and adverse vents (AE):

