#### Potential serious adverse events (SAEs) not directly related to the trial and adverse events (AEs)

Children’s schooling or parent/guardians’ work is adversely affected (e.g. due to time spent in therapy or assessments encroaching on school or homework time).One or more aspect of the therapy or assessment procedure induces unacceptable levels of distress for either the participant, their parent/guardian, or the therapist.It becomes apparent that one or more of the exclusion criteria is met (or inclusion criteria not met) by the participant. [NB. This will be logged but the participant remains in treatment as long as clinically appropriate and retained in the intent to treat sample.]A sustained and significant increase in detrimental behaviours (e.g. safety-seeking behaviours) as determined by any of the outcome measures collected throughout the study.The emergence of new detrimental behaviours (e.g. self-harm).Drop-out of treatment/request to change therapist (all routinely monitored for the presence of AEs).A complaint is received from a participant, their parent/guardian, or the therapist referring to an actual or perceived adverse event as defined above.

The window for reporting SAEs and AEs will be:(i)During the treatment phase based on therapist report(ii)Up to the end of study based on parent report (i.e. up to the 26-week assessment or qualitative interview, whichever is later).

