The 14-week and 26-week assessments will include questionnaires to monitor participants’ functioning and quality of life; therefore, information on some of the potential adverse events identified in this document will be routinely collected. Therapists will also be asked to indicate the presence of an SAE or AE that arises during the course of treatment. Further investigation will be made by the clinical team and the PI and the SAE/AE procedures will be followed where applicable. Specifically, the clinical team and the PI will assess the frequency and severity of the adverse event(s) and determine whether the participant should be withdrawn from the trial. The decision of the clinical team will be followed in the event that a consensus is not reached. Participants will also be given the opportunity to report adverse events anonymously after the parent and child complete questionnaires at 14 and 26 weeks and in person (remotely) after the qualitative interviews (for the parents). The research team will regularly review responses to identify any responses that indicate the presence of an adverse event and will report summaries of these responses to the Trial Steering Committee for review.

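### The rule that turns repeated AE reports into SAEs conflicts with the protocol's own definition of seriousness, so SAE counts would mix serious with merely repeated events

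*Protocol article*

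**What the plan says.** Under Definition of serious adverse events, the protocol article opens with "A serious adverse events (SAE) is any untoward medical occurrence that" and lists outcomes: death, threat to life, hospital admission or prolonged stay, lasting or significant disability, and congenital anomaly. The only extension is for important medical events. These "may also be considered a serious adverse event when, based upon appropriate medical judgement, the event may jeopardise the participant", which is a judgement on the single case. The same section states: "There is a very low risk of SAEs in the current trial". The next section gives trial-specific examples of SAEs, such as psychiatric admission, suicidal behaviour or a new mental health diagnosis. None of this text uses frequency as a criterion.

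The section on potential SAEs not directly related to the trial and AEs then lists further items. Examples are that "schooling or parent/guardians’ work is adversely affected", that a complaint is received, or "Drop-out of treatment/request to change therapist (all routinely monitored for the presence of AEs".

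Under Reporting procedures for adverse events/serious adverse events, the rule for any AE is that, when it "is reported more than once for a participant, or more than three times during the study, it will be treated as an SAE". The same section limits reports to the ethics committee to SAEs that the Chief Investigator judges both related and unexpected.

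Reports come from several sources. Therapists report during treatment. On the questionnaires, "Participants will also be given the opportunity to report adverse events anonymously after the parent and child complete questionnaires at 14 and 26 weeks". Parents who are interviewed have a further opportunity.

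**The concern.** Two sections of one document assign events to the same category by different principles. One looks at what happened to the participant. The other looks at how many reports were received. An AE that meets none of the seriousness criteria, and that nobody judges medically important, still enters the SAE category on its second report for a participant or on the fourth report in the study.

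What is at stake is the harms reporting. An SAE total is normally read as a count of events with grave outcomes. Under this rule it would also contain events whose only distinguishing feature is repetition. In a trial that expects very few SAEs, a handful of escalated AEs could make up much of the total.

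**Working it through.** **1. The texts side by side**

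| | Definition section | Reporting procedures |
|---|---|---|
| Criterion | Outcome, or an important medical event | Number of reports |
| Severity needed | Yes | No |
| Case-level judgement | Yes, for important medical events | None |
| Depends on other participants | No | Yes, for the study-wide count |

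Both cannot determine the same category. An item such as schooling affected by time spent in therapy fails the first column and can pass the second.

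**2. Reports, not events**

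The rule counts how often an AE is reported. One mild, persistent problem noted at both 14 and 26 weeks, or by both parent and therapist, meets the more-than-once condition without recurring. Reports made anonymously may not be linkable to a participant, so the per-participant condition may not be assessable for them. The article does not say whether the first three reports of a type are reclassified once the fourth arrives.

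**3. The study-wide limit against the size of the trial**

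*Inputs*
- N = 418 to 560, from Sample size {14}.
- Trigger: more than three reports, that is four or more, from Reporting procedures.
- AE incidence p per participant: not given in the document. Assumed range 0.1% to 2%.

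*Check of N.* The margin is 0.33 SD, power is 80% or 90%, and attrition is 30% (Sample size {14}). One-sided alpha is 0.025, from the 95% confidence limit in Analysis of clinical outcomes. The true difference is taken as zero. The formula per arm is n = 2(z_alpha + z_power)² / 0.33², divided by 0.70 for attrition.
- 80% power: 2 × 7.849 / 0.1089 = 144.2, so 145. Then 145 / 0.70 = 207.1, so 208 per arm and 416 in total (stated: 418).
- 90% power: 2 × 10.507 / 0.1089 = 193.0, so 193. Then 193 / 0.70 = 275.7, so 276 per arm and 552 in total (stated: 560).

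Both are close to the stated figures. N serves here only as the denominator, and no sample-size figure is disputed.

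*Formula.* Let X be the number of participants reporting a given AE type, with one report each and independence, so X ~ Binomial(N, p). Then P(X ≥ 4) = 1 − Σ C(N,k) p^k (1−p)^(N−k), summed over k = 0 to 3.

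*Example.* For N = 418 and p = 0.01, the four terms are 0.0150, 0.0632, 0.1332 and 0.1866. Their sum is 0.398, so P(X ≥ 4) = 0.602.

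| Assumed incidence | Expected participants, N = 418 / 560 | P(X ≥ 4), N = 418 / 560 |
|---|---|---|
| 0.1% | 0.42 / 0.56 | 0.1% / 0.3% |
| 0.5% | 2.09 / 2.80 | 16% / 31% |
| 1% | 4.18 / 5.60 | 60% / 81% |
| 2% | 8.36 / 11.2 | 97% / 99.6% |

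The trigger is reached with 50% probability at an incidence of 0.88% (N = 418) or 0.66% (N = 560), and with 95% probability at 1.85% or 1.38%. Four participants are 4/418 = 0.96% or 4/560 = 0.71% of the sample.

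The same AE rate therefore has a different chance of escalation at the two ends of the planned sample-size range. The table counts one report per participant, so repeat reports can only raise these probabilities.

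**The case against.** The strongest defence is that the sentence stands under a reporting heading and says only that such an AE is to be handled like an SAE. On that reading it is a cautious escalation rule that leaves the definition intact. It errs towards over-reporting, and every event that meets the definition is still captured. The article states no SAE rate and no comparison of SAEs between arms, and tabulation is commonly left to the analysis plan. The AE list also contains grave items, such as emerging self-harm.

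Much of this stands, and it limits the point. A reader might go further in four ways that the documents do not support:

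- **That SAE counts become meaningless, or that true serious events are buried.** Events meeting the definition are still recorded and can be tabulated separately.
- **That the 30% attrition allowance shows the limit would be far exceeded.** That figure is a sample-size allowance, not an AE rate. The list says treatment drop-outs are monitored for AEs, which need not mean that each one is an AE.
- **That the ethics committee would be flooded.** Only events judged related and unexpected go there. The clinical team and the investigator assess frequency and severity, and the steering committee reviews summaries of participants' responses.
- **That SAE rates would differ between arms for non-safety reasons.** The rule is the same in both arms and the study-wide count is pooled. The article gives no figures from which a difference could be sized.

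The conflict itself remains. The escalation reading is possible, but the article does not state it, and it does not say that escalated AEs are kept apart from events that meet the definition.

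**Conclusion.** The point holds: the reporting rule is wrong as written, with moderate severity. Followed literally, it places repeated but non-serious events in the SAE category, contrary to the protocol's own definition. SAE counts would then mix the two kinds and be hard to interpret.

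How often this happens cannot be derived from the document, because no AE incidence is given. If an AE type affects about 2% of families, escalation by the study-wide count is almost certain. At 1% it is more likely than not, at 0.5% it is a minority outcome, and at 0.1% it is very unlikely. These results assume independent participants and one report each. The per-participant trigger adds to them by an amount that cannot be calculated here.

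Randomisation, the primary outcome, the non-inferiority margin and the efficacy analysis are not touched.

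**What to change.** Reconcile the definition and the reporting procedures. SAE status should follow the criteria under Definition of serious adverse events. Repetition of an AE, within a participant or across the study, should trigger review by the trial management group and the steering committee. The event stays an AE unless that review finds that it meets the criteria.

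In any case, log and tabulate by arm the events that meet the definition separately from AEs escalated on frequency alone. This can still be done although the stated end of recruitment is 03/08/2022, because it needs only a flag on each logged event.

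The cost is a wording change, a field on the safety log and one extra table. No safety information is lost.

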### Frequency and plans for auditing trial conduct {23}

The study may be monitored, or audited in accordance with the current approved protocol, GCP, relevant regulations, and standard operating procedures. In addition, a risk assessment will be carried out and provided to the CTRG before the study opens and will be reviewed as necessary over the course of the study to reflect significant changes to the protocol or outcomes of monitoring activities (e.g. monitoring of adverse events).

### Plans for communicating important protocol amendments to relevant parties (e.g. trial participants, ethical committees) {25}

Following Sponsor approval, the protocol, informed consent form, participant information sheet, and any proposed advertising material will be submitted to an appropriate Research Ethics Committee (REC), HRA, and host institutions for written approval. The Investigator will submit and, where necessary, obtain approval from the above parties for all substantial amendments to the original approved documents. For protocol modifications, we will first seek approval from the TSC and then apply for approvals as required.

### Dissemination plans {31a}

A summary of the study findings will be circulated at the end of the study to all participating clinical teams and families. Peer-reviewed publications will be produced to reach a wider audience.

## Discussion

This study has been designed to be a pragmatic trial embedded in the services which would be the typical users of this type of brief intervention for child anxiety problems. This is a definite strength of the trial design, as it maximises the likelihood that the results will reflect the outcomes that could be expected in clinical practice outside of a trial. Designing the trial to be almost entirely managed using online platforms will enable us to have large numbers of trial sites spread across the UK, and to involve clinical teams who have previously not taken part in the research.

If non-inferiority is found, the research will provide the following: (1) a solution for efficient psychological treatment for child anxiety disorders while social distancing (for the current context and future pandemics); (2) an efficient means of treatment delivery as ‘normal service’ resumes to enable CAMHS to cope with the anticipated increase in referrals when social distancing measures are relaxed and schools re-open; and (3) a demonstration of rapid, high-quality evaluation and application of online interventions within NHS CAMHS to drive forward much-needed further digital innovation and evaluation in CAMHS settings. The primary beneficiaries will be children with anxiety problems and their families, NHS CAMHS teams, and commissioners who will access a potentially effective, cost-effective, and efficient treatment for child anxiety problems.

### Limitations and barriers

Conducting a trial during the COVID pandemic is challenging. From a structural perspective, support during this period for clinical teams taking part in the trial may not always be available, and also an increased, and in many cases more severe, number of referrals is likely to put significant pressures on clinical teams. We are reliant on parent and child reports of treatment outcomes and do not have the capacity to conduct systematic clinical assessments within the trial procedures. We are also reliant on clinical teams and families to confirm inclusion/exclusion criteria; however, this does mean that the participants reflect families who would likely be offered the novel intervention within routine clinical services.

### Trial status

Protocol V2.3, 15.07.2022

Recruitment start date: 05/12/2020

End date for recruitment 03/08/2022

## Data Availability

The final trial dataset will be accessed by the trial statisticians and health economist. There are no contractual agreements in place that limit access for investigators. Anonymised quantitative trial data will be made available for open access on completion of the trial.

## Abbreviations

AE: Adverse event
AES-256: Advanced Encryption Standard - 256
AHSN: Academic Health Science Networks
AnDY: Anxiety and Depression in Young People Research Clinic (University of Reading)
CAIS-C: Child Anxiety Impact Scale—Child
CAIS-P: Child Anxiety Impact Scale—Parent
CAMHS: Child and Adolescent Mental Health Services
CBT: Cognitive Behavioural Therapy
CEA: Cost-effectiveness analysis
CEI: Credibility and Expectation of Improvement Scale
CHU-9D: Child Health Utility
CI: Chief Investigator
Co-CAT: Child Anxiety Treatment in the context of COVID-19
Co-SPACE: COVID-19: Supporting Parents, Adolescents and Children during Epidemics
COVID-19: Coronavirus disease 2019
CRF: Case Report Form
CSRI: Client Services Receipt Inventory
C-TAU: Treatment as Usual in the context of COVID-19
CTRG: Clinical Trials & Research Governance, University of Oxford
CUA: Cost-utility analysis
CYP: Children and young people
DHSC: Department of Health and Social Care
DMEC: Data Monitoring and Ethics Committee
DMP: Data Management Plan
eCRF: Electronic Case Report Form
EQ-5D-5L: European Quality of Life-5 Dimension 5 - Level (adult quality of life instrument)
ePRO: Electronic Patient-Reported Outcome
GBO: Goal-based outcomes—goal progress chart
GCP: Good Clinical Practice
GDPR: General Data Protection Regulation
GP: General Practitioner
HRA: Health Research Authority
HTTPS: Hypertext Transfer Protocol Secure
IAPT: Improving Access to Psychological Therapies
ICER: Incremental Cost-Effectiveness Ratios
ICF: Informed consent form
ICMJE: International Committee of Medical Journal Editors guidelines
IRAS: Integrated Research Application System
IP: Internet Protocol
ISF: Investigator Site File
ISRCTN: International Standard Randomised Controlled Trials Number
ITT: Intention to treat
MRC: Medical Research Council
MSD: Medical Science Division
NHS: National Health Service
NICE: The National Institute for Health and Care Excellence
OID: Organisational Information Document
OSI: Online Support and Intervention (for child anxiety)
PC-CTU: Primary Care Clinical Trials Unit
PI: Principal Investigator
PIL: Participant/Patient Information Leaflet
PPI: Patient and Public Involvement
Q&A: Question and answer
QALYS: Quality-adjust life years
RCADS-C/P: Revised Children’s Anxiety and Depression Scale – Child/ Parent
RCT: Randomised controlled trial
R&D: NHS Trust R&D Department
REC: Research Ethics Committee
REDCap: Research Electronic Data Capture
RES: Research Ethics Service
SAE: Serious adverse event
SAP: Statistical analysis plan
SCAS-P8: Brief Spence Children’s Anxiety Scale-Parent Version
SDQ-p: Strengths and Difficulties Questionnaire- parent report
SOE: Schedule of events
SOP: Standard Operating Procedure
SPIRIT: Standard Protocol Items: Recommendations for Interventional Trials
SRS: Session Rating Scale
SSL: Secure Socket Layer Encryption
TAU: Treatment as usual
TMG: Trial Management Group
TSC: Trial Steering Committee
UKRI: UK Research and Innovation
VAS: Visual Analogue Scale
